### Participants

#### Recruitment

The population base from which the subjects will be drawn are Dutch non-treatment seeking frequent cannabis users, meeting all inclusion and none of the exclusion criteria. For the purpose of the trial, a website is created containing information about the study and the possibility to register as a potential participant. To ensure the recruitment of the planned number of participants targeted Facebook and Instagram campaigns will be used. We have experienced that this is a very effective strategy for the recruitment of cannabis users. In 2018, we conducted an exploratory online survey among frequent cannabis users [25]. In just a few months the online campaigns resulted in the recruitment of more than 1000 eligible participants for the survey study. In this study protocol, “he” is used to refer to a participant; however, where “he” is stated, “he or she” is meant.

#### In- and exclusion criteria

In order to be eligible to participate in the study, a subject must meet all of the following criteria:
Age 18+Cannabis use on 3 or more days a week in the past 3 monthsDesire to reduce or quit cannabis useSmartphone availableAbility and intention to participate in the training and study for the period of 6 monthsInformed consent provided

A potential subject who meets any of the following criteria will be excluded form participation in this study:
Formal treatment (psycho-social or pharmacological) for cannabis use or any other substance use in the past 3 monthsInsufficient mastery of the Dutch languageSelf-reported suicidal ideation, acute psychosis, or severe depressionPregnant or lactating

#### Sample size

For the RCT, conventional power (1-*β* = 0.80) and levels of statistical significance are chosen (*α* = .05, 2-sided). The meta-analysis conducted by Boumparis et al. revealed a small but significant effect in favor of digital prevention interventions compared to control conditions, an effect size of g = 0.33 was found [14]. However, the effect size of our online SBIRT program is expected to be somewhat larger due to the fact that the brief intervention is only one component of the program. The referral to treatment component may also have some effect on cannabis consumption. The referral to treatment component consists of information about specialized treatment services for substance use problems. Participants are encouraged to utilize these services. When participants enter treatment, it is likely that this will also have an effect on their cannabis consumption. Therefore, we expect an effect size of *d* = 0.4 or more. G*Power was used to calculate the required number of participants. The power calculation is based on 2-sided-tests, *d* = 0.40 corresponds with a sample size of at least 2 × 100 participants. Assuming a 25% non-response at 6 months’ follow-up, we aim to include at least (100/(100–25)) × 100 × 2 = 267 participants. In case the dropout is higher than expected, this number may be adjusted upwards.

### Intervention condition

The experimental ICan intervention is designed according to the SAMHSA Screening Brief Intervention and Referral to Treatment (SBIRT) framework and is based on cognitive behavioral therapy (CBT) and motivational interviewing (MI). The participant receives an e-mail with an invitation to create an account. The ICan intervention includes adherence-focused guidance. From the moment the participant creates an account, he receives a weekly WhatsApp message from a coach to encourage him to use the app. In the first message(s), the participant is encouraged to complete the self-test and to create the reduce/quit plan. In the subsequent message(s), the participant is encouraged to fill in the consumption diary regularly. Besides the WhatsApp messages, the participant receives motivational push notifications. The participant can set up reminders to fill in the consumption diary. He can indicate how often he would like to receive the reminders and at what time. After 4 weeks, the participant is asked if he is satisfied with the progress he has made so far. If he is not satisfied he is referred to specialized treatment services (see part 4). After these 4 weeks, the WhatsApp messages are discontinued—unless the participant explicitly indicates that he wants to keep receiving the messages. In that case, he receives a weekly message in which he is praised for his achievements in the app—for example completing the additional problem solving exercise, posting a message on the peer support platform, or filling in the consumption diary. The participant keeps receiving these messages as long as he is actively using the app.

#### ICan part 1: screening

The screening procedure consists of four short self-tests.
*How is your cannabis consumption compared to others?* The participant answers a set of questions about his cannabis use. Based on his answers, personalized normative feedback (PNF) is given. PNF aims to correct the misperception that the use of substances is common among people of the same peer group as the participant. The amount of money that the participant can save by quitting his cannabis use is calculated (per week, month, and year).*What type of cannabis user are you?* The second test is based on the Marijuana Motives Measure [26]. The test assesses six motives for using cannabis: enhancement, coping, social, conformity, expansion, and routine. The average score on the six subscales/motives is provided to the participant.*How risky is your cannabis use?* This third test is based on the ASSIST [27]. The participant answers six questions about his cannabis use in the past 3 months. Based on his answers, a personalized feedback report about the risks associated with his cannabis use is provided. Participants at risk for cannabis use-related problems are advised to reduce or quit their cannabis use. The emphasis lies on the health gains that can be achieved by reducing or quitting their cannabis use. Participants at severe risk for cannabis use-related problems are advised to seek specialized treatment. However, if a participant is still hesitant about reducing his cannabis use and/or seeking help, he also gets the option to complete the online training (first).*Are you “addicted” to cannabis?* The fourth and last test is based on the Cannabis Use Disorders Identification Test Revised (CUDIT-R) [28]. The participant answers 8 questions about his cannabis use in the past 6 months. Based on his answers, feedback is given about the risk for cannabis use disorder. Cannabis users at moderate or severe risk for cannabis use disorder are advised to reduce or stop their cannabis use. They are referred to the ICan (web) app for further information about cannabis use disorder and specialized treatment services.

#### ICan part 2: brief intervention (I)

After the self-test is completed, an introduction slider is displayed with the main features of the app. The main features are the homepage, consumption diary, reduce/quit plan, personal profile page, peer support platform, and treatment info pages.

The brief intervention component helps participants to create a personalized plan to stop or reduce their cannabis use step by step. The steps (with the exception of step 3b) are based on the protocol for brief cognitive behavioral treatment for substance use disorders [29].
Step 1: Motivation to change. The participant first lists the advantages of using cannabis; then, he lists the disadvantages of using cannabis and the advantages of reducing or quitting. Based on these lists, the participant decides whether he wants to continue his cannabis use or wants to reduce/quit.Step 2: Setting a goal. The participant determines whether he wants to reduce or quit his use and picks a quit date.Step 3a: How to achieve your goal. The participant identifies high-risk situations: situations, thoughts, and/or feelings that trigger a strong craving to use cannabis. A short animation video explains how self-control strategies can be applied to prevent cannabis use. Subsequently, the participant describes how he will apply these strategies to deal with high-risk situations in the future.Step 3b: How to solve problems. If a participant experiences problems (e.g., financial problems) that may negatively impact his ability to reduce or stop cannabis use, he can do an additional exercise in which he learns how to solve problems step-by-step.Step 4: Social support. The participant describes how his friends, acquaintances, and/or loved ones can support him during his reduce/quit attempt. He lists the names of the persons he wants to ask for support.Step 5: Withdrawal symptoms, craving, and relapse. The participant is informed about withdrawal symptoms. A short animation video provides tips on how to deal with craving. The participant describes how he wants to deal with craving and relapses.Step 6: Your personal (quit) plan. By completing step 1 through 5, the participant has created a personal reduce/quit plan, this plan is summarized in step 6.

#### ICan part 3: brief intervention (II)

From the set (quit) date, the participant is encouraged to stick to his (quit) plan. Based on the entries in the cannabis consumption diary, automatic tailored feedback is given. On the personal profile page, a bar graph shows the progress made by the participant. Icons are used to show in which situations (time of day, type of activity, in the presence of which emotion/feeling, alone or with others) the participant is most likely to experience craving and in which situations he is most likely to use cannabis. The number of days without cannabis use and the amount of money saved are also displayed on this page. The participant is advised to stick to his personal (quit) plan for at least 4 weeks.

After 4 weeks, the participant evaluates if he is satisfied with the progress he has made so far. If desired, a new goal can be set. Participants who fail to stick to their plan are referred to specialized treatment services (see part 4). If a participant is reluctant to engage in specialized treatment, he can continue to use the ICan (web)app.

#### ICan part 4: referral to treatment

The referral to treatment component consists of comprehensive information on specialized treatment services for substance use problems. The information is summarized in a short animation video. Participants can easily check which treatments are offered nearby based on their location/zip code.

#### Peer support platform

On the peer support platform, participants can write messages to motivate and support each other.

#### Badges

The participants can earn badges for their achievements in the app. The earned badges are displayed on the badge page.

### Control condition

The control condition consists of four online modules of educational information on cannabis. In the first module, some background information about cannabis is provided. This includes information on the physical and mental effects of cannabis, commonly used consumption methods and cannabis and the law. In the second module, the risks associated with cannabis use are listed. Some tips on how to reduce these risks are given. In the third module, general information about cannabis use disorder is provided. The difference between physical and psychological dependence is explained. The negative social, financial, and health consequences of cannabis use disorder are described, and the DSM-5 criteria for cannabis use disorder are presented. In the last module, some general tips on how to reduce or quit cannabis use are provided. The information used in the four online modules is based on the websites www.drugsinfo.nl and www.drugsenuitgaan.nl. The general tips on how to reduce or quit cannabis use are from an existing information brochure about cannabis use and psychosis [30]. Since the control condition consists of information that is currently available online for non-treatment seeking frequent cannabis users, we considered this to be the standard care (or treatment-as-usual).

### Outcome measures

#### Primary measures

Figure 2 shows the SPIRIT diagram of the trial. The primary outcome measure is the number of cannabis use days in the past 7 days, assessed 6 months post randomization using the Timeline Follow-back (TLFB) method [31]. The TLFB method is originally developed as an interview to assess self-reported alcohol consumption [31]. Growing evidence suggests that the TLFB is a psychometrically sound measure for the assessment of licit and illicit substance use [32]. Self-reports on cannabis use measured using the TLFB method show high test-retest reliability [33]. TLFB reports administered online are consistent with TLFB reports administered face-to-face [34].

**Fig. 2 Fig2:**
[figure not shown]
SPIRIT diagram. Schedule of enrollment, allocation, interventions, and assessments. TLFB, Timeline Follow-back; CUDIT, Cannabis Use Disorders Identification Test; DSM-5, number of DSM-5 criteria met (self-reported); MHSAS, Mental Help Seeking Attitudes Scale; ZUF-8, Fragebogen zur Messung der Patientenzufriedenheit; TiC-P, Trimbos and iMTA questionnaire on Costs associated with Pychiatric illness; SF-6D, ShortForm 6 Dimensions; MCQ-SF, Marijuana Craving Questionnaire Short Form; CSCS, Cannabis Self-Concept Scale; MCSDS, Marlowe-Crowne Social Desirability Scale; BSI-18, Brief Symptom Inventory 18

#### Secondary measures

##### Cannabis use, cannabis use disorder, and cannabis use-related problems

The following secondary outcome measures will be applied (see also Fig. 2):
The number of cannabis use days in the past 7 days assessed using the TLFB method 6 weeks post randomization and 3 months post randomization.The quantity of cannabis used (grams) in the past 7 days assessed using the TLFB method 6 weeks post randomization, 3 months post randomization, and 6 months post randomization. Participants are first asked to indicate how many joints they usually make from a single gram of cannabis. Next, they are asked to fill out the calendar. They indicate, for each of the 7 days listed on the calendar, how many joints they smoked. If they smoked only half a joint on a particular day, they are asked to fill-in ½. Based on the number of joints made from a single gram and the number of joints smoked, the quantity of cannabis used (grams) is calculated. Van der Pol et al. [35] validated different self-report measures on cannabis dose against objective measures. Self-reported number of joints per gram was one of the least problematic options.Cannabis use-related problems as measured using the Cannabis Use Disorders Identification Test (CUDIT), a 10-item questionnaire based on the Alcohol Use Disorders Identification Test [36].The cannabis use disorder severity, as measured by the number of self-reported DSM-5 criteria met [37].Number of self-reported previous serious attempts to reduce or quit cannabis use. A serious quit attempt is defined as an attempt that lasted at least 24 h.

##### Treatment seeking behavior and attitudes

f)Help seeking attitudes as measured by the Mental Help Seeking Attitudes Scale (MHSAS) [38]. MHSAS is a 9-item questionnaire designed to assess the overall attitude towards seeking help (unfavorable–favorable) from a mental health professional if one had to deal with a mental health problem. Each item is rated on a 7-point-scale. We adapted the questionnaire to measure attitudes towards seeking professional help specifically for cannabis use-related problems.g)Based on Ajzen’s Theory of Planned behavior, we constructed a questionnaire to assess intention, social norm, perceived behavioral control, and attitudes towards seeking professional help for cannabis use-related problems.h)The Trimbos and iMTA questionnaire on Costs associated with Pychiatric illness (TiC-P) will be used to measure the number of participants who entered specialized treatment services for cannabis use-related problems 3 months and 6 months post randomization [39]. Some questions are added to determine whether participants visited a specific health care professional for cannabis use-related problems, for other problems or for both. Complementary, participants are presented with a list of more informal types of help (e.g., seeking help from a religious confidant, seeking help from a loved one, seeking help online) and are asked to indicate whether they used any of these types of help in the past 3 months.

##### Intervention satisfaction

i)Intervention satisfaction is measured with the Dutch translation of the Fragebogen zur Messung der Patientenzufriedenheit (ZUF-8) [40]. The ZUF-8 is a free-to-use German version of the Client Satisfaction Questionnaire (CSQ-8). The questionnaire consists of 8 items; each item is rated on a 4-point-scale. The ZUF-8 has good psychometric properties [41].

##### Cost-effectiveness

j)The Trimbos and iMTA questionnaire on Costs associated with Pychiatric illness will be used to measure health care utilization and production loss (TiC-P) [39].k)Quality of life will be measured using the SF-6D [42].

##### Mediators and other measures

The following instruments will be applied to assess their potential role as intervention effect mediator:
l)The number of self-reported cannabis withdrawal symptoms.m)Craving for cannabis will be assessed using the Marijuana Craving Questionnaire Short Form (MCQ-SF) [43].n)The Cannabis Self-Concept Scale (CSCS) will be included to assess identification with cannabis as part of one’s personality or identity [44].o)Self-efficacy to become or stay a non-cannabis smoker will be measured by 6 items used in previous research [45].p)The Marlowe-Crowne Social Desirability Scale (MCSDS) will be included to measure if the respondent has the tendency to give socially desirable responses [46].q)The Brief Symptom Inventory 18 (BSI-18) will be included to assess symptoms of anxiety and depression [47].r)Self-reported substance use (tobacco, alcohol, cocaine, amphetamine, inhalants, sedatives, hallucinogens, opioids, and other drugs).s)Utilization measures will be collected during the use of the intervention: number of logins, number of page views, time spent logged in, and use of major content elements.t)Demographic characteristics of the participant will be collected such as age, sex, and level of education.u)Knowledge obtained about CBT principles will be measured with a self-constructed 5-item questionnaire.v)Knowledge obtained about treatment options/referral to treatment will be measured with a self-constructed 5-item questionnaire.w)The effect of the coronavirus and the coronavirus measures on cannabis use and attempts to reduce/quit cannabis use will be measured with a self-constructed 7-item questionnaire.

### Statistical analyses

Conventions with regard to the analysis of the data and reporting of the study will be followed, in this case the CONSORT statement guidelines [24]. We recognize the importance of open data initiatives and intend to—under conditions—open the anonymized datasets collected in this research project to whoever is professionally interested and entitled to use these data, as long as it is acceptable to the research participants and ethical standards. Generalized linear mixed models (GLMM) will be applied to the primary and secondary outcome measures. Time will be modeled as a categorical variable. Depending on the data, we will use random slopes. When there is a lot of variation in the number of cannabis use days at baseline—we expect this will be the case—then we will at least fit a random intercept. The link function of the GLMM will be chosen depending on the data: most likely this will be a binomial distribution in the case of dichotomous outcome measures, Gaussian in the case of normally distributed data and (overdispersed) Poisson or negative binomial for count data. Covariates in the model will be variables that differ at baseline (*p* < .05) and the MCSDS. Missing data is expected to be missing at random and will be handled using the Multivariate Imputation via Chained Equations (MICE) package in R.

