### Study procedures

Figure 1 shows the CONSORT flow diagram of the trial. Applicants interested to participate fill out an online screening questionnaire to determine if they meet all of the inclusion criteria and none of the exclusion criteria. Applicants who are eligible to participate receive the patient information letter and the informed consent form. Participants have up to 30 days to decide if they want to participate. If they have any questions regarding the study or intervention, they can contact a member of the research team by phone, email, or face-to-face. They can also contact an independent expert whose contact details are listed in the patient information letter. Applicants who decide to participate in the study are asked for necessary personal data. After the participants have sent us their signed informed consent form digitally, they are directed to the baseline questionnaire. The electronic data capture platform Castor will be used for the randomization and allocation procedure and to conduct the online questionnaires. The research data are stored separately from the participants’ personal data. Only the four authors of this study protocol will have access to the keys to join the research data tables with the personal data tables. After the participants have completed the baseline questionnaire, they will be allocated to one of two trial arms (1:1) using variable block randomization. Participants will be informed that they will be assigned to one of two programs, both focusing on cannabis moderation. Depending on the outcome of the allocation procedure, an email will be sent to the participants containing an access code to either the ICan intervention or the online control program (four online modules of educational information on cannabis). Participants will be blind to the condition they are in.

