## Discussion

This paper describes the protocol to test the effectiveness of an Internet-based intervention with adherence-focused guidance on reducing cannabis use and improving positive attitudes towards seeking professional help in a sample of frequent cannabis users via a two-armed randomized controlled trial. To the best of our knowledge, this is the first Internet-based intervention for cannabis users that combines screening, a brief intervention based on CBT and MI, and referral to treatment.

All outcome measures in this study are based on self-report questionnaires, not on biological measures such as hair or urine samples. It is not possible to determine whether participants will truthfully report their cannabis use or will give socially desirable answers. As mentioned before, the TLFB method is a psychometrically sound measure for the assessment of licit and illicit substance use [32]. Research has shown that the TLFB method for the detection of substance use, including cannabis use, has high levels of overall agreement with biological measures [32]. To control for potential socially desirable answers, the MCSDS will be included.

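### Apart from the MCSDS, model covariates are chosen by a baseline significance test, so chance decides the adjustment set and baseline cannabis-use days are rarely a covariate

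*Protocol article*

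**What the plan says.** The Statistical analyses section plans one model family for every outcome: "Generalized linear mixed models (GLMM) will be applied to the primary and secondary outcome measures". On time it says "Time will be modeled as a categorical variable", without saying whether T0 is one of the response levels. The covariate rule is explicit: "Covariates in the model will be variables that differ at baseline", judged at p < .05, plus the MCSDS. The Discussion gives the reason for the one fixed covariate: "To control for potential socially desirable answers, the MCSDS will be included".

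Baseline use days appear in the model description only as the trigger for a random intercept ("When there is a lot of variation in the number of cannabis use days at baseline"), not as a named covariate. Under Outcome measures, the primary endpoint is the same quantity at 6 months: use days in the past 7 days by Timeline Follow-back.

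The Study design section places T0 before randomisation. On allocation, Study procedures says "they will be allocated to one of two trial arms (1:1) using variable block randomization"; no stratification on baseline use is mentioned. For the sample size, "The power calculation is based on 2-sided-tests", with d = 0.40, 100 per arm and 267 in total after 25% non-response. No gain from covariates is assumed.

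**The concern.** Adjusting for a covariate helps when that covariate predicts the outcome. A test comparing the arms at baseline does not measure that. T0 is recorded before a 1:1 random allocation, so the null hypothesis of that test is true by design and p < .05 marks a chance event.

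Two things follow. The primary model cannot be written down until the baseline data have been tested, and what enters has no systematic link to prognosis. The variable with the best claim to be adjusted for, the same measure taken before randomisation, gets no special place, whereas the MCSDS does. (That baseline use is strongly prognostic is a statistical judgement about a repeated measure. The article does not say so.) The rule also applies to all the secondary models.

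This is not a detail left for an analysis plan to supply. The article fixes the rule, so the rule has to be withdrawn.

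**Working it through.** **Inputs from the article.** d = 0.40, two-sided α = .05, power 0.80, 100 per arm evaluable, 25% non-response (Sample size); screen at p < .05 (Statistical analyses).

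**Inputs assumed, because the article does not give them.** Number of baseline variables screened, k = 15 to 30, treated as independent; correlation ρ between baseline and 6-month use days, 0.3 to 0.7; normal outcome, one follow-up.

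**1. The plan's own figure.** The two-sample noncentral t calculation with d = 0.40 gives power just under 0.80 at 99 per arm and 0.804 at 100 per arm. Then 200 / (1 − 0.25) = 266.7, rounded up to 267. Both stated figures reproduce.

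**2. How often the screen selects something.** Each variable passes with probability 0.05. Expected number selected = 0.05k; P(at least one) = 1 − 0.95^k.
- k = 15: 0.75 expected; 1 − 0.95^15 = 0.54.
- k = 30: 1.5 expected; 1 − 0.95^30 = 0.79.

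Baseline use days, as any single variable, pass about 5% of the time and are left out as a covariate about 95% of the time.

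**3. Power at d = 0.40 and 100 per arm.** Divide d by the square root of the relative variance v and use the same t calculation:
- follow-up only: v = 1
- baseline always adjusted: v = 1 − ρ²
- change-type contrast (T0 a response level, arm means free at T0, equal SDs): v = 2(1 − ρ)

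Worked case, ρ = 0.5: adjusted, 0.40/√0.75 = 0.462, power 90%; change-type, 0.40/√1 = 0.40, power 80%.

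| ρ (assumed) | Follow-up only | Baseline always adjusted | Change-type contrast |
|---|---|---|---|
| 0.3 | 80% | 84% | 66% |
| 0.4 | 80% | 87% | 73% |
| 0.5 | 80% | 90% | 80% |
| 0.6 | 80% | 94% | 88% |
| 0.7 | 80% | 98% | 95% |

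The change-type contrast is never better than adjustment, since 2(1 − ρ) − (1 − ρ²) = (1 − ρ)² ≥ 0.

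**4. The stated rule itself, simulated.** Single follow-up, 100 per arm, adjusting for baseline only when its own test gives p < .05. Power is about 0.80 at ρ = 0.3 and about 0.82 at ρ = 0.7. Type I error falls from about 0.048 at ρ = 0.3 to about 0.036 at ρ = 0.7. The test is slightly conservative.

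**The case against.** The strongest reply is that nothing planned is lost. The sample size assumes no covariate gain and reproduces exactly. In the single-follow-up simulation the rule keeps power at 80% to 82% and type I error below 0.05. The screen looks only at baseline data and is declared in advance, and the MCSDS is in the model whatever the tests show. All of this stands. The cost is therefore limited to forgone precision and a model left to chance. At ρ = 0.3 the gain forgone is modest, about 4 percentage points (80% to 84%).

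A second reply is that if T0 is a response level, baseline use is already in the model and the random intercept takes account of part of it. That also stands, so a reader should not infer that baseline use is ignored altogether. Only its role as a covariate depends on the screen.

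A reader might go further and infer that the plan falls below its stated 80% power. The 66% and 73% entries in the table would suggest this, but the article does not support it. Those figures need T0 in the response, free arm means at T0, equal SDs and ρ of 0.4 or less, none of which is stated. From ρ = 0.5 the same contrast gives 80% or more. The eligibility floor of 3 use days a week may also narrow the baseline spread. With a baseline SD 0.6 times the follow-up SD (assumed), v = 1 + 0.36 − 1.2ρ, which gives 80% power at ρ = 0.3 and 85% at ρ = 0.4.

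**Conclusion.** The concern holds as a badly fixed analysis rule. The chance-driven selection follows from randomisation alone. The 54% to 79% figure depends on the assumed 15 to 30 independent tests. The forgone power, about 4 to 18 percentage points against a follow-up-only comparison, depends on the assumed ρ of 0.3 to 0.7 and on a normal, single-follow-up approximation to the planned GLMM.

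A reader might infer inflated false positives or an invalid sample size. Neither is shown: 100 per arm and 267 in total are correct for their stated inputs, and the rule errs on the conservative side. If T0 is in the response and baseline use also happens to pass the screen, it would be outcome and covariate at once. That requires both an unstated model choice and a roughly 5% event, so it is a reason to specify the model and not a demonstrated error.

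**What to change.** Replace the covariate sentence in Statistical analyses as follows:
- Delete the p < .05 rule.
- Prespecify baseline 7-day use days in the primary model in one of two ways, not both: as a covariate in a model for T1 to T3, or with T0 in the response and the arm means constrained equal at T0.
- Keep the MCSDS or justify it, and state that its baseline value is used.
- For secondary outcomes, adjust for the baseline value only where the outcome is measured at T0. Intervention satisfaction, for example, has no baseline value.
- Report baseline characteristics by arm without significance tests.

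The cost is a few lines of text, settled before the outcome data are analysed. Recruitment is already complete, but the change needs no new data and no change to the sample size.
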